### Intervention

All participants will undergo an 8-week intervention. All participants will receive 6 physiotherapy sessions within 8 weeks, while the rTMS + PiP and sham rTMS + PiP groups will receive 11 additional rTMS sessions in the same period. Figure 2 shows the intervention timeline for the active rTMS + PiP and sham rTMS + PiP groups, while Figure 3 shows the intervention timeline for the UP group. A detailed description of each intervention is provided below.

**Figure 2 figure2:**
[figure not shown]
Intervention timelines for the active rTMS + PiP and sham rTMS + PiP groups. Each bar represents a session of intervention. A black bar represents an rTMS (or sham) session offered at the research center, while a grey bar represents a physiotherapy session offered in one of the local clinics. PiP: psychologically informed physiotherapy; rTMS: repetitive transcranial magnetic stimulation.

**Figure 3 figure3:**
[figure not shown]
Intervention timelines for the usual care group. Each bar represents a physiotherapy session provided in one of the participating local clinics. In the first 4 weeks, 4 sessions were offered at 1-week interval. In the last 4 weeks of the intervention, 2 additional sessions were offered at 2-weeks interval.

#### Active rTMS

Participants will receive 11 sessions of rTMS. For the first 2 weeks, participants will attend 5 brain stimulation sessions that will serve as an induction phase to optimize the effects of rTMS [41]. During weeks 3 to 8, 6 rTMS sessions will be provided, once per week. Each rTMS session will last 30-40 minutes (10-20 min of installation + 20 min of stimulation). Stimulation parameters will be obtained by measuring the motor threshold of the right first dorsal interosseous muscle, and then the rTMS intensity will be set at 110% of this motor threshold [32,42]. High-frequency rTMS consisting of 60 trains of 5 seconds at 10 Hz with 15-second intertrain intervals, for a total of 3000 pulses per session, will be used [32]. High-frequency rTMS has been shown to reduce chronic pain [32] and depression symptoms [43]. The coil will be positioned over the left dorsolateral PFC by using the BeamF3 methods [44].

#### Sham rTMS

For the sham stimulation, a sham coil looking like the regular rTMS coil but with a magnetic shield blocking the magnetic field will be used to produce the auditory effects and vibration similar to the active coil. This type of sham has been shown to be effective to blind participants [32]. All other parameters will be the same as the active rTMS.

#### PiP Intervention

The objective of PiP is to identify the biopsychosocial factors that may impede recovery and to address these factors within the physiotherapy scope of practice. To standardize PiP delivery, treating physiotherapists providing PiP will receive a 2-day training provided by an expert in PiP who also has expertise with military personnel. They will learn to use strategies such as the establishment of common goals and therapeutic alliance, the use of the behavior change model, motivational interviewing approach, education on pain neuroscience, gradual exposure to movement, and stress management strategies (eg, breathing techniques, meditation) [45]. The training will also include a section on the military culture to foster therapeutic alliance with veterans and optimize the treatment adherence. It provides foundational knowledge about the Canadian Armed Forces, including its branches, core values, and professional expectations. It supports participants in understanding how military culture influences health behaviors and offers guidance on how this awareness can inform clinical assessments and interventions with veterans. These physiotherapists will also be allowed to use standard physiotherapy modalities presented in the UP section, based on their clinical judgement. However, they will be encouraged to assess and address psychosocial factors by using strategies learned during their training. This training has been shown to be effective in leading to changes in the clinical practice of physiotherapists, leading to a greater use of modalities targeting psychological factors compared to UP [45]. Participants in the PiP + active rTMS and PiP + sham rTMS groups will have access to a website offering support information on topics such as pain neuroscience education, common myths and misconceptions about back pain, the psychological factors influencing pain, self-management strategies, and healthy lifestyle habits (eg, sleep and nutrition). This site will be freely available to participants during the study. Physiotherapists will be asked to discuss one topic at each session with the participants to assess and reframe (if necessary) their conceptualization of these concepts.

#### UP Intervention

This pragmatic group aims to represent real-world clinical practice, including interventions commonly used in physiotherapy to manage CLBP. No training will be provided, and all modalities typically used by physiotherapists in the province of Quebec will be allowed, including but not limited to manual therapy, active exercises, education, stretching, etc. Each physiotherapy session, including PiP and UP, will last between 30 and 45 minutes. Physiotherapists providing UP and PiP will all complete a checklist to indicate the interventions provided at each treatment session.

### Outcomes

#### Overview

All PROMs will be assessed and filled online by using REDCap. Sociodemographic information will first be collected before randomization. PROMs baseline measurements will be measured after randomization, just prior to the beginning of the treatment. This decision was taken because the time before care initiation can vary depending on the groups (rTMS vs no rTMS) and the clinics delivering the different physiotherapy approaches (PiP vs UP). A longer delay before care initiation for a specific group may influence the outcomes trajectories. The baseline primary outcome will be measured 48 hours prior to the beginning of treatment. Nonetheless, the primary outcome will also be collected before randomization (during enrollment for screening purpose) to ensure similar between-group evolution until baseline measurement. However, participants will be informed on their allocated groups only after baseline PROMs to avoid any anticipation bias. PROMs will then be measured again via email to participants at 2, 8, and 26 weeks after the first treatment session. Figure 4 presents the SPIRIT diagram of this study.

**Figure 4 figure4:**
[figure not shown]
SPIRIT (Standard Protocol Items: Recommendations for Interventional Trials) diagram. PiP: psychologically informed physiotherapy; rTMS: repetitive transcranial magnetic stimulation.

#### Primary Outcomes

The primary outcome will be physical functioning, which will be evaluated using ODI, a 10-item questionnaire (0=no disability; 100=extremely severe disability) that is valid and reliable and recommended to evaluate physical functioning in LBP [46]. The primary time point will be at 8 weeks.

#### Secondary Outcomes

The average pain intensity over the last week will be assessed with the 11-point numerical pain rating scale (0: “no pain” to 10: “worst pain you can imagine”). The numerical pain rating scale is reliable and responsive to change and recommended in LBP trials [46]. The quality of life will be measured using the EQ-5D-5L, which is a generic questionnaire evaluating five dimensions of health-related quality of life, each rated on a 5-point scale [47]. Depression symptoms will be measured using the Patient Health Questionnaire (9 items), which is reliable and valid [48]. Pain catastrophizing will be measured using the valid and reliable Pain Catastrophizing Scale [49]. Movement pain–related fear will be assessed with the Tampa Scale of Kinesiophobia questionnaire (13 items), which has good reliability and validity [50]. Self-efficacy will be measured using the Pain Self-Efficacy Questionnaire, which is valid, reliable, and responsive to change in a population with CLBP [51]. Medication use will be measured using the Medication Quantification Scale Version IV that quantifies 22 drug classes used in pain management (eg, opioid) with a detriment weight [52]. Posttraumatic stress disorder symptoms will be assessed with the Posttraumatic Stress Disorder Checklist for Diagnostic and Statistical Manual of Mental Disorders, which is a 20-item self-report questionnaire that is consistent and valid [53]. The Patient Acceptable Symptom State will be used to determine if the participants consider their current functional and symptom states as satisfactory or not. In addition, the Global Rating of Change, an 11-point scale ranging from –5 (a great deal worst) to 5 (a great deal better) will be used to measure the perceived change of health status after the intervention (ie, at 8 weeks and 26 weeks). Finally, all adverse events and reasons for drop-out will be recorded and reported.

#### Analysis

##### Sample Size Calculation

The trial is designed to detect a 9-point (SD 10) between-group difference in physical functioning at 8 weeks, as measured using the minimal important difference of the ODI [54]. The standard deviation was estimated from our previous RCTs [45,55]. Considering 20% loss at follow-up, 1-β=.90, and α=.05, 32 participants per group will be recruited (n_total_=96).

#### Statistical Analysis

A linear mixed model will be used to compare treatment effects on outcomes, using intention-to-treat analyses. Group (active rTMS + PiP, sham rTMS + PiP, and UP) and time (baseline, 2, 8, 26 weeks) will be entered as fixed factors, participants as random intercept, and stratification factors (gender and baseline ODI score) as covariate, to determine the presence of any significant group × time interaction. Missing values will be handled with multiple imputations if necessary, and sensitivity analyses will be completed to confirm/infirm the results.

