## Methods

### Study Design

This protocol is reported according to the SPIRIT (Standard Protocol Items: Recommendations for Interventional Trials) guidelines [37]. Participants included in this 3-arm, parallel-group RCT will be randomized to one of the 3 groups (PiP + active rTMS, PiP + sham rTMS, or UP) and will undergo an 8-week intervention. Outcomes measurements will occur at baseline, 2, 8, and 26 weeks after the beginning of the intervention (Figure 1). The protocol of this RCT has been registered on ClinicalTrials.gov (NCT06999772).

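### The only covariance term stated is a random intercept; without an added residual structure, standard errors rest on equal variance and correlation across visits at 0, 2, 8 and 26 weeks

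*Protocol article*

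**What the plan says.** The Statistical Analysis section plans a linear mixed model by intention to treat. Group has three levels, and "time (baseline, 2, 8, 26 weeks) will be entered as fixed factors". The dependence between a participant's measurements is described in one phrase, "participants as random intercept, and stratification factors", the latter (gender and baseline ODI) being covariates. The purpose is "to determine the presence of any significant group × time interaction". The section names no random slope, residual covariance, robust standard error or degrees-of-freedom method. It promises sensitivity analyses without giving their content.

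The Study Design section gives the visits: "Outcomes measurements will occur at baseline, 2, 8, and 26 weeks after the beginning of the intervention". Under Primary Outcomes, "The primary time point will be at 8 weeks". The only SD in the article is in the Sample Size Calculation, where the trial is meant to "detect a 9-point (SD 10) between-group difference in physical functioning at 8 weeks".

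**The concern.** A random intercept with ordinary residuals (independent, equal variance) is compound symmetry: the same variance at each visit and the same correlation for each pair. The gaps between visits are 2, 6 and 18 weeks, so the model gives baseline and week 2 the same correlation as baseline and week 26. Repeated scores usually correlate less as time passes. Variances may also change, because entry requires an ODI of at least 15% and participants may then respond differently to treatment.

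If the true pattern differs, one pooled within-person variance serves contrasts that have different true variances. Confidence intervals are then too wide at some visits and too narrow at others. An early effect could be missed, and a lasting effect at week 26 could be declared too readily. The main estimate at week 8 would rest on an assumption that nothing in the article supports.

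**Working it through.** **The plan's own figure.** Inputs: difference 9, SD 10, "Considering 20% loss at follow-up, 1-β=.90, and α=.05"; two-sided testing is assumed. Per group, 2 × (10 × (1.960 + 1.282) / 9)² = 25.94, so 26. Then 26 × 1.2 = 31.2, rounded up to 32, and 3 × 32 = 96 as stated. (Dividing by 0.8 gives 32.5, so 33.) This is a two-sample comparison at week 8 that uses no within-person correlation, so the covariance question does not affect it.

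**Formula.** Take complete data, the full group × time model, and a contrast between two groups in change from baseline. Per participant:
- Variance the random-intercept model uses: 2 × (mean variance − mean covariance), averaged over the four visits and six pairs.
- True variance at visit j: Var(0) + Var(j) − 2 Cov(0, j).
- SE ratio (model / true) = √(model variance / true variance).
- Type I error = 2 × (1 − Φ(1.96 × SE ratio)).

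**Worked case (assumed values).** SD 10 throughout. Correlations with baseline are .8, .6 and .5; weeks 2–8, 2–26 and 8–26 are .7, .6 and .7. Mean covariance = (80 + 60 + 50 + 70 + 60 + 70) / 6 = 65, so the model variance is 2 × (100 − 65) = 70.

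| Visit | True variance | SE ratio | Type I error |
|---|---|---|---|
| Week 2 | 2 × (100 − 80) = 40 | √(70/40) = 1.32 | .010 |
| Week 8 | 2 × (100 − 60) = 80 | √(70/80) = 0.94 | .067 |
| Week 26 | 2 × (100 − 50) = 100 | √(70/100) = 0.84 | .101 |

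With 32 per arm, the week-8 model SE is √(2 × 70/32) = 2.09 and the true SE is √(2 × 80/32) = 2.24. A simulation of 20,000 complete trials agreed: type I error .069 at week 8 and .101 at week 26, empirical SD 2.24 at week 8.

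Varying the three correlations not involving baseline:
- All .6: mean covariance 61.67, model variance 76.67, type I error .055 at week 8 and .086 at week 26.
- All .7: mean covariance 66.67, model variance 66.67, type I error .074 and .110.

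**Range over other assumed covariances (closed form).** The AR(1) rows run by visit order.

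| Correlation; SDs at 0/2/8/26 weeks | Week 8 ratio (type I) | Week 26 ratio (type I) |
|---|---|---|
| Constant .6; 10 throughout | 1.00 (.050) | 1.00 (.050) |
| AR(1) .7; 10 throughout | 0.92 (.072) | 0.81 (.113) |
| AR(1) .8; 10 throughout | 0.92 (.073) | 0.79 (.124) |
| AR(1) .7; 10/11/12/14 | 0.99 (.052) | 0.79 (.123) |
| Baseline .73/.58/.43; 10 throughout | 1.04 (.041) | 0.90 (.079) |
| Baseline .73/.58/.43; 10/11/12/14 | 1.13 (.026) | 0.88 (.086) |
| Constant .6; 10/12/14/14 | 1.01 (.047) | 1.01 (.047) |

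In every row with falling correlation the week-2 ratio exceeds 1 (1.20 to 1.49).

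**With dropout.** REML simulations used 32 per arm, 20% missing at week 8 and 25% at week 26, with 250 runs each. Type I error at weeks 8 and 26 was .040 and .056 (first row), .088 and .124 (second row), and .044 and .108 (sixth row). The Monte Carlo error is about .01 to .02.

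**Overall interaction.** Under the worked case, the overall group × time test, which the section names as its target, rejected in about 6–8% of null trials.

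**The case against.** The article fixes less than it may seem to. A random intercept can be combined with a structured or heterogeneous residual matrix. The residual structure and degrees-of-freedom method are commonly left to an analysis plan, which is not shown here. This stands in part: leaving those details out is no fault. But the article does choose a dependence term, and as written with ordinary residuals that term means compound symmetry. The point is about that choice.

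A reader might infer that the planned model certainly gives wrong standard errors, that the week-8 interval will be too narrow, and that week 26 is always worse. The documents support none of these. They give one SD and no correlations. Compound symmetry produces no error if it is true. The pooled variance averages short and long gaps, so week 8 can come out near zero error or conservative. With constant correlation and SDs 10/12/14/14, weeks 8 and 26 have the same ratio.

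The promised sensitivity analyses could address the matter, but with no stated content they cannot be counted on.

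**Conclusion.** The point holds as a conditional weakness in a stated choice, not as a demonstrated error. That a random intercept with ordinary residuals imposes equal variance and equal correlation is certain. How much this matters depends on assumed covariances.

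If correlations decay, week-26 type I error was about 8–12% in the cases tried and the week-2 standard error was too large. At week 8 the range was about 2.6–7.4%, and about 6.7–6.9% with SD 10 and baseline correlations .8/.6/.5. The direction at week 8 cannot be known before the data are seen. That is the reason not to depend on it: an anti-conservative error inflates false positives, and a conservative one spends power in a trial sized for 90%. With 20% loss expected, estimates that rely on data missing at random also lean on the covariance being right. The change is worth making.

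**What to change.** Replace the random intercept with an unstructured within-participant covariance, fitted by REML with Kenward-Roger degrees of freedom, and otherwise keep the fixed effects. State which outcome vector is meant:
- Baseline stays an outcome, as the section now has it: four visits, 10 covariance parameters.
- Baseline is used only as a covariate: three post-baseline visits, 6 parameters. Time then has three levels, and the treatment effect is a baseline-adjusted group difference at each visit, so this is a change of model beyond the covariance.

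Name the fallback in advance in case of non-convergence: heterogeneous Toeplitz, or a structure that respects the unequal spacing.

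The random-intercept model has 2 covariance parameters, so the change adds 8 or 4 and leaves slightly fewer degrees of freedom; 96 participants can support either. Sample size, recruitment and conduct are unchanged. Follow-up is planned to run to December 2027, so there is time to fix this before analysis.

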### Randomization and Blinding

A randomization list will be generated using a computer random number generator by blocks of 3, 6, or 9 by an independent research assistant. The randomization list will be uploaded on a Research Electronic Data Capture (REDCap, Vanderbilt University) platform by using the randomization module. Once the randomization list will be uploaded, REDCap will automatically retrieve the group allocation. This method digitally replicates the allocation concealment and prevents selection bias without having to manipulate sealed envelopes. Randomization will be stratified by self-reported gender and physical functioning (ODI score ≤ or > 40).

To ensure that no assessor could bias data collection, all patient-reported outcome measures (PROMs) will be assessed using REDCap. Although it is not possible to blind participants to a physical intervention (UP and PiP), they will be blinded to rTMS group allocation (active vs sham). The rTMS intervention will be delivered at the research center, and the physiotherapy interventions will be delivered in local physiotherapy clinics. The 2 interventions (PiP or UP) will be provided in 2 different physiotherapy clinics, reducing the risks of potential group contamination. Furthermore, the physiotherapists providing PiP will not be informed of the type of rTMS (sham vs active), and participants will be asked not to discuss rTMS sessions with their treating physiotherapist. The statistician will be blinded to group allocation. Overall, the RCT will be triple-blind for rTMS (ie, participants, treating physiotherapist, statistician) and single-blind for physiotherapy (ie, statistician). At week 8, participants in the PiP groups will be asked to determine which stimulation they believed they received (sham, active, or don’t know) and to provide the reasons for their choice through a blinding evaluation questionnaire. At any time during the trial, if any severe adverse event occurs (ie, seizure), the research team and the participant will be informed of its group allocation to appropriately manage this event.

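### The baseline ODI covariate does not match the ODI used to stratify, and as a main effect it drops out of the group × time contrast that serves as the primary test

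*Protocol article*

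**What the plan says.** Four places in the protocol article bear on this point.

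- **Statistical Analysis, response and test.** Group and "time (baseline, 2, 8, 26 weeks) will be entered as fixed factors", with "participants as random intercept". The purpose is "to determine the presence of any significant group × time interaction".
- **Statistical Analysis, covariates.** The model adds "stratification factors (gender and baseline ODI score) as covariate". It does not say whether ODI enters as a continuous score or dichotomized.
- **Randomization and Blinding.** "Randomization will be stratified by self-reported gender and physical functioning (ODI score ≤ or > 40".
- **Outcomes, Overview.** "PROMs baseline measurements will be measured after randomization, just prior to the beginning of the treatment". The same paragraph places the baseline ODI 48 hours before treatment, says that a separate ODI is collected before randomization for screening, and says that participants learn their group only after the baseline questionnaires.

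The Sample Size Calculation is set to "detect a 9-point (SD 10) between-group difference in physical functioning at 8 weeks". That is a between-group difference at one visit, not an interaction.

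**The concern.** Two things look wrong. First, a stratification factor must be known when the patient is randomized. In this protocol the baseline ODI is not yet known then, so it cannot be the stratification factor that the analysis section calls it. If the words are taken literally, the same measurement is also both the first response and a predictor of that response.

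Second, adjustment for the baseline value of the primary outcome is normally where a trial of this size gains precision. Entered as a main effect in a model that already holds baseline as a response and tests group × time, it adds no precision to that test. At stake are the efficiency of the primary test and, under one reading of the covariate and some dropout patterns, its freedom from bias.

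**Working it through.** **1. The plan's own sample size.** Inputs from the Sample Size Calculation: difference 9, SD 10, power 0.90, α 0.05 (taken as two-sided), 20% loss.

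n per arm = 2 × (1.960 + 1.282)² × 10² / 9² = 25.9, so 26 evaluable. Inflation gives 26 × 1.2 = 31.2 (32), or 26 / 0.8 = 32.5 (33). The stated 32 is reproduced. With 32 × 0.8 = 25.6 completers per arm, power is 0.896. No covariate enters this calculation.

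**2. Which ODI?** Stratification needs a value before randomization. The Overview gives two ODI measurements: screening (before) and baseline (after). Only the first can define the stratum. The analysis section attaches the name of the second to the role of the first.

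**3. Cancellation.** Write the planned model for person i in group g at visit j as

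Y_ij = μ + γ_g + τ_j + (γτ)_gj + βX_i + b_i + e_ij.

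In the change from baseline to week 8, βX_i and b_i both subtract out. With complete data the week-8 interaction estimate is therefore the difference in mean change, whatever X is. In simulation of this model (random intercept, REML, 3 × 32, SD 10), estimates with no ODI covariate, continuous baseline ODI, baseline ODI > 40 and screening ODI > 40 agreed to within 1e-12.

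**4. Cost in precision.** Let r be the correlation of baseline with week 8. The documents do not give it, so a range is shown. SD 10 is assumed to be the SD of scores at each visit.

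- Change-score variance per person: 2σ²(1 − r)
- Baseline-adjusted variance per person: σ²(1 − r²)
- Ratio, adjusted to change: (1 + r)/2

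At r = 0.6 with 32 per arm, the SE is √(2 × 100 × 0.8 / 32) = 2.24 for change and √(2 × 100 × 0.64 / 32) = 2.00 for the adjusted comparison. Evaluable n per arm for 90% power is 25.9 × 2(1 − r) or 25.9 × (1 − r²), rounded up. Power uses 25.6 completers per arm and the normal approximation.

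| r | Variance saved by adjustment | n per arm, change | n per arm, adjusted | Power, change | Power, adjusted |
|---|---|---|---|---|---|
| 0.3 | 35% | 37 | 24 | 78% | 92% |
| 0.5 | 25% | 26 | 20 | 90% | 96% |
| 0.6 | 20% | 21 | 17 | 95% | 98% |
| 0.7 | 15% | 16 | 14 | 99% | 99% |

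At r = 0.5 the change score has the same variance as the raw score, so the planned power is kept. Below 0.5 the change contrast falls short of it.

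**5. Missing data.** If X is the continuous baseline ODI, one slope is forced across visits, although the slope on itself is 1 at baseline and about r at week 8. The covariate also absorbs between-person variance: in simulation the ratio of intercept to residual variance fell from about 1.5–2.4 to 0.2–0.4. The model then makes less use of a dropout's earlier visits. Simulated results, with about 20% dropout before week 8, no imputation, and dropout running in opposite directions in two arms:

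- Dropout driven by baseline ODI, true effect 9, equal correlation between visits of 0.4, 0.6 and 0.8: mean estimate 10.07, 9.81 and 9.36 with continuous baseline ODI; 9.07, 9.10 and 8.98 with no covariate; 9.08, 9.09 and 8.99 with the screening stratum. The covariate adds 1.00, 0.71 and 0.38 points.
- Dropout driven by early change, no true effect, equal correlation 0.6: bias of 0.9 to 1.1 points in absolute size, with type I error of 6.2% where it was recorded. With correlation decaying over time (0.8): bias 1.2 points and type I error 11%, against 0.4 points and 6% for a follow-up-only model.
- Dropout acting alike in all arms: no visible bias (8.91 with the covariate, 8.92 without, at 0.6).

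Under decaying correlation (0.75, true effect 9) the model without any ODI covariate already gave 9.60, the screening stratum 9.71 and continuous baseline 10.08. Most of that shift therefore comes from the random-intercept structure, and about 0.5 from the covariate.

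**The case against.** The strongest reply is that the governing words are stratification factors. On that reading the model adjusts for the screening stratum, loosely labelled baseline. Nothing is then both response and predictor, and the added bias in step 5 essentially disappears. This stands: a reader might infer that the covariate is definitely the post-randomization score, but the text does not settle it. The mismatch between sections and the cancellation in step 3 remain under either reading.

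A reader might also infer that the adjustment is useless throughout. It is not. The model-based week-8 group difference, which is the quantity that was powered, does gain precision: at correlation 0.6 its SD falls from 2.48 to 1.95 with continuous baseline ODI, about the same as an analysis of covariance. For the secondary outcomes ODI is not a response level. But the section names only the interaction as the test.

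A third inference would be that the primary result is biased as planned. The documents give no dropout pattern, and they provide for multiple imputation if necessary and for sensitivity analyses. Imputed data sets are complete, so by step 3 the covariate would leave the contrast unchanged and any bias would depend on the imputation model.

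Nor does measuring baseline after randomization show bias in itself, since participants are not told their group until afterwards. Finally, a model with baseline as a response level is valid; the loss is one of efficiency, and at r of 0.5 or more the planned power is kept or nearly so.

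**Conclusion.** The point holds in limited form and should be fixed. The protocol calls baseline ODI a stratification factor when, on its own timing, it cannot be one. With complete data the ODI covariate, whichever value is meant, has no effect on the group × time contrast. The primary test as written is a change-score comparison whose variance exceeds that of a baseline-adjusted week-8 comparison by a factor of 2/(1 + r): 1.33, 1.25 or 1.18 at r = 0.5, 0.6 or 0.7. These values rest on an assumed r and on equal variance at the two visits.

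Bias of roughly 0.4 to 1.2 ODI points, against a target of 9, is a conditional risk. It needs the continuous post-randomization baseline as covariate, analysis of incomplete data without imputation, and dropout that differs by arm. The documents do not support calling the planned analysis biased outright.

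**What to change.** State in the Statistical Analysis section which ODI enters the model and in what form, and bring Randomization and Blinding and the Outcomes overview into line with it. Then choose one of two models:

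1. Response at weeks 2, 8 and 26 only, with continuous pre-treatment ODI and its interaction with time, plus gender and the screening ODI stratum (≤ or > 40) as randomized.
2. Response at baseline and weeks 2, 8 and 26, with a common baseline mean across arms, no baseline ODI covariate, and adjustment for gender and the screening ODI stratum.

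In either case, name the between-group difference at week 8 as the primary contrast, to match the primary time point and the sample size statement.

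The cost is wording. Both ODI measurements and gender are already collected, and the 32 per arm stands. The Results section expects follow-up to run to December 2027, so there is time to settle this before the data are analysed.

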Therefore, the main objective of this study will be to compare the effectiveness of (1) combining PiP + active rTMS, (2) PiP + sham rTMS, and (3) UP alone in improving the physical functioning in veterans experiencing CLBP and comorbid psychological factors. The secondary objectives will be to compare their effectiveness on pain intensity, quality of life, movement pain–related fear, pain catastrophizing, self-efficacy, depressive symptoms, medication use, and posttraumatic stress disorder symptoms. We hypothesize that the combination of active rTMS + PiP will result in a larger effect on primary and secondary outcomes compared to PiP + sham rTMS and UP alone. In addition, we hypothesize that PiP with active rTMS or sham rTMS will be more effective than UP.

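### The only test named is an overall group × time interaction (6 df), whereas the primary time point, sample size and hypotheses concern pairwise group differences, with week 8 as the time point

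*Protocol article*

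**What the plan says.** In the protocol article, the Statistical Analysis section describes a linear mixed model by intention to treat. The first fixed factor is "Group (active rTMS + PiP, sham rTMS + PiP, and UP"; the second is described as "time (baseline, 2, 8, 26 weeks) will be entered as fixed factors". Participant is a random intercept and the stratification factors are covariates. The stated inferential aim is "to determine the presence of any significant group × time interaction". No contrast, order of comparisons or step after the interaction test is given.

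Three other places describe a narrower question:

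- Primary Outcomes: "The primary outcome will be physical functioning, which will be evaluated using ODI", and "The primary time point will be at 8 weeks".
- Sample Size Calculation: "The trial is designed to detect a 9-point (SD 10) between-group difference in physical functioning at 8 weeks".
- Hypotheses, at the end of the Introduction: active rTMS with PiP is expected to have a "larger effect on primary and secondary outcomes compared to PiP + sham rTMS and UP alone", and PiP with either stimulation is expected to do better than UP. The Abstract says the same. These are pairwise and directional. They do not themselves name week 8; the primary time point and the sample size supply it.

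**The concern.** The article does name a test, and that test does not correspond to the question it calls primary. An interaction over all groups and visits is significant when any arm departs from any other at any follow-up visit. It gives week 8 no special weight and has no direction.

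Two claims are at stake. One is the week-8 claim: an early difference at week 2, near the end of the rTMS induction phase, or a late one at week 26, can produce a significant interaction with nothing at week 8. The other is the rTMS claim: an effect of PiP alone, shared by the active and sham arms, can also produce it. With no primary contrast fixed, a significant interaction leaves three arm pairs at three follow-up visits, nine differences in all, from which a headline result could be chosen.

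**Working it through.** **Inputs from the article.** Three groups; four visits; difference 9 ODI points; SD 10; alpha 0.05 (two-sided assumed); power 0.90; 20% loss; 32 per group. Completers per arm: 32 × 0.8 = 25.6.

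**Assumed.** The within-person correlation r is not given, so 0.3, 0.5 and 0.7 are shown. Correlation is taken as equal between all visits, which is what a random intercept implies. Tests are asymptotic.

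**1. What the stated sample size describes.** For two means, n = 2(1.96 + 1.2816)² × 10² / 9² = 25.94, so 26 evaluable per arm. Then 26 × 1.2 = 31.2, rounded up to 32, which matches the article (26 / 0.8 = 32.5 would give 33). The planned size is therefore that of one unadjusted two-arm comparison at one visit, with 1 df.

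**2. What the named test is.** Interaction df = (3 − 1) × (4 − 1) = 6. Two of these concern the change from baseline to week 8; the other four concern weeks 2 and 26. The critical value of chi-square on 6 df at 5% is 12.59.

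**3. Significant interaction with no week-8 effect.** The noncentrality is λ = n × Σ c′V⁻¹c over groups, where c is a group's change-from-baseline vector minus the mean over groups. Under equal correlation V = 100(1 − r)(I + J), with inverse (I − J/4) / [100(1 − r)].

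For one arm differing by 9 points at week 2 only:

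- Centring over three groups gives (2/3)² + 2(1/3)² = 2/3.
- The visit pattern gives 81 × (1 − 1/4) = 60.75.
- λ = 25.6 × (2/3) × 60.75 / [100(1 − r)] = 10.368 / (1 − r).

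| r | λ | P(interaction significant) |
|---|---|---|
| 0.3 | 14.81 | 84% |
| 0.5 | 20.74 | 95% |
| 0.7 | 34.56 | 99.8% |

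Every week-8 contrast stays at its 5% level. A 9-point effect at week 26 only gives the same λ.

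**4. Significant interaction with no rTMS effect.** Let both PiP arms beat UP by 9 points at weeks 2, 8 and 26, with active equal to sham. The group factor is again 2/3, and the visit pattern gives 3 × 81 − 27²/4 = 243 − 182.25 = 60.75. λ and the rejection rates are therefore those in the table, while the active-versus-sham contrast stays at 5%.

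**5. Power against a week-8 contrast.** The SE of a week-8 difference in change is 10 × √[4(1 − r)/25.6]. At r = 0.5 this is 2.795, so z = 9 / 2.795 = 3.22 and power is 90%. For the interaction at r = 0.5:

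| Pattern (difference at weeks 2 / 8 / 26) | λ | Interaction power | Week-8 contrast for 9 points |
|---|---|---|---|
| One arm, 0 / 9 / 0 | 20.74 | 95% | 90% |
| One arm, 9 / 9 / 9 | 20.74 | 95% | 90% |
| Active vs UP 3 / 9 / 6, sham halfway | 11.52 | 72% | 90% (active vs UP) |

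The sign of the gap depends on the pattern, and none of these patterns is in the article.

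**6. Cost of multiplicity.** With Bonferroni over three contrasts the critical value is 2.394, and at r = 0.5 the power for 9 points is Φ(3.22 − 2.394) = 80%. By the same formula it is 63% at r = 0.3 and 96% at r = 0.7.

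**The case against.** The strongest reply is that this is analysis-plan detail which an article may leave out. The article fixes the outcome, the time point and the comparisons, and says the model will be used to compare treatment effects. A model with categorical time and a group × time term is the one that yields week-8 contrasts. On this view only the sentence naming them is absent, and a plan not shown may contain it.

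Part of this stands. The model need not change, and the missing contrasts alone would not be a finding. But the article is not silent on inference. It names a test, and that test does not match its own primary question. A plan that named week-8 contrasts would still leave this wording to be reconciled.

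Two stronger readings are tempting and not supported. A reader might infer that success will be declared on the interaction p-value; the article never says so. A reader might also infer that spreading the test over 6 df costs power in general. The last table above shows that it does in some patterns and not in others. Moreover, setting the interaction against one unadjusted contrast is not like for like once several contrasts are confirmatory.

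**Conclusion.** The point holds as a mismatch between the named test and the stated question. A significant interaction does not establish a week-8 difference, nor an effect of active over sham rTMS; a non-significant one does not settle either question. On the stated SD and completer number, and assuming equal within-person correlation of 0.3 / 0.5 / 0.7, the interaction is significant in about 84% / 95% / 99.8% of trials when the only effect is 9 points in one arm at week 2. The same rates apply when both PiP arms beat UP by 9 points at every follow-up visit and rTMS adds nothing. The 6 df and the text comparison need no assumption; the percentages depend on the correlation and on the effect patterns chosen for illustration. No general loss of power is claimed.

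**What to change.** In the Statistical Analysis section:

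- Make the primary analysis the model-estimated week-8 differences in ODI with 95% CIs, from the same mixed model with time categorical.
- State before analysis which of the three pairwise contrasts (active + PiP vs sham + PiP, active + PiP vs UP, sham + PiP vs UP) are confirmatory, and how alpha is handled, for example by a fixed testing order or Bonferroni.
- Report the overall interaction, week 2 and week 26 as secondary.

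In the Sample Size Calculation section, say that the 90% power applies to a single unadjusted week-8 contrast.

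The cost is wording, with no new data; the article expects follow-up to finish in December 2027, so there is time. The downside is the alpha rule. A fixed order keeps about 90% for the first contrast (at correlation 0.5), but later ones can be tested only if the earlier ones succeed. Bonferroni over three brings each to about 80%. Restoring 90% would need 2(2.394 + 1.2816)² × 100 / 81 = 33.4, so 34 evaluable, or 34 / 0.8 = 42.5, so 43 per arm.
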